#### Sample size calculation

Since the primary objective of the study is to determine the side effect profile of IRE, the sample size is powered on a common event; erectile dysfunction. *Ahmed* et al. performed three comparable studies with a concurrent focal ablation modality (HIFU), and a similar patient population and the same primary objectives [33–35]. Focal ablation with HIFU led to a decline of 18.2 % on the IIEF-15 questionnaire (57.5 % to 47.0 % after 12 months). Converting this to the shortened IIEF-5 questionnaire (which is used in this RCT), the mean IIEF score is 16.61 (SD 4.0) in Group A (focal ablation) and the mean IIEF score is 15.1 (SD 4.0) in Group B (extended ablation). A two group Wells-Satterthwaite *t*-test of equal means and unequal variances were used to calculate the sample size. The one-sided (one-tailed) test was used, because this rejects the null hypothesis for differences in a single direction. With an α level of 0.05 and power of 80 % (1-β), the sample size required was at least 90 men per group. The sample size was adjusted to allow for 35 % of men in the general population (>50 years old) having poor baseline erectile function [36], and therefore aim to recruit at least 200 men in total.

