## Methods/Design

### Study objectives

#### Primary

To evaluate the differences in side effects of patients treated with focal vs extended ablation of PCa with IRE, measured by CTCAE, IIEF, IPSS and use of pads.To evaluate the differences in quality of life of patients treated with focal vs extended ablation of PCa with IRE, measured by EPIC, VAS pain score and length of hospital stay.

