### Randomization, sample size and statistical analysis

#### Randomization

The patients are stratified on baseline total IIEF-score with cut-off score of 45 points (≤45 vs. >45), Gleason score (grouped in Gleason sum score 6 vs. sum score 7) and age with cut-off score of 60 years (≤60 and >60) to prevent randomly occurring differences in important prognostic factors across the two randomized groups. Patients are blinded to the randomized treatment given (focal or extended ablation) to ensure unbiased assessment. The treating physicians have to be informed about the actual treatment in order to be able to perform the ablation. mpMRI findings will be coded and centrally assessed by a uro-radiologist, blinded for the results of TTMB and the performed procedure.

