#### Statistical analysis

Data will be collected using the Data Management System of CROES. The validated questionnaires will be analysed with standard methods. Maximum and minimum values will be set according to the extremes of questionnaire item scales. Categorical outcomes will be reported as point estimates with binomial 95 % CIs to demonstrate level of precision. Wilcoxon signed rank test (two-tailed) will be used to assess differences between continuous variables that were not normally distributed (PSA and questionnaire scores), measured at baseline and at the subsequent follow-up visit. Changes over time will be reported with box-and-whisker plots. The group analyses will be hypothesis-generating and we will run statistical tests of significance.

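### The IIEF comparison is sized as if men with poor baseline erectile function do not inform it, but the objective and analysis set no such limit, and 200 men reach 80 % power only if those men carry most of the effect

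*Protocol article*

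**What the plan says.** Under Sample size calculation, the article says that "the sample size is powered on a common event; erectile dysfunction". It assumes a mean IIEF-5 of 16.61 with focal ablation and 15.1 with extended ablation, SD 4.0 in both groups. It states that "The one-sided (one-tailed) test was used", with α 0.05 and 80 % power, and arrives at 90 men per group. It then adds: "The sample size was adjusted to allow for 35 % of men in the general population (>50 years old) having poor baseline erectile function", and sets the target at 200 in total.

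Elsewhere these men stay in:

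- **Primary objective:** "To evaluate the differences in side effects of patients treated with focal vs extended ablation of PCa with IRE, measured by CTCAE, IIEF, IPSS" and pad use. No limit by baseline function is given.
- **Table 1:** no inclusion or exclusion criterion concerns erectile function.
- **Randomization:** "The patients are stratified on baseline total IIEF-score with cut-off score of 45 points", so low scorers are randomised by design.
- **Statistical analysis:** a two-tailed signed rank test is named for non-normal variables ("PSA and questionnaire scores), measured at baseline and at the subsequent follow-up visit"). No subset is named, and the group analyses are called hypothesis-generating.

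**The concern.** The allowance for poor baseline function treats those men as lost to the IIEF comparison, in the way one allows for dropout. Nothing in the objective, eligibility, randomisation or analysis then takes them out. The article recognises the problem and deals with it only by headcount.

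If men with little function to lose are compared along with the rest, and they show a smaller arm difference, the average difference shrinks. Stratifying on baseline IIEF balances them between arms but does not undo that. A small IIEF difference would then be hard to interpret: it could mean that extended ablation costs little more function than focal ablation, or that many men compared had little to lose. This touches the outcome on which the trial is sized. If the population is chosen only after results are seen, the choice is open to the data. The Background section itself reports earlier IRE erectile outcomes among men who were potent before treatment.

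**Working it through.** **Inputs.** From Sample size calculation: difference 16.61 − 15.1 = 1.51; SD 4.0; one-sided α 0.05; 90 per group; 200 in total; 35 % with poor baseline function. Assumed: 1:1 allocation (100 per arm), and f, the fraction of the arm difference that poor-function men show.

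**Plan's base figure.** n = 2(1.645 + 0.842)² × 4.0² / 1.51² = 87 per group; the exact t-test gives 88. At 90 per group, exact power is 81 %. The stated 90 reproduces.

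**Allowance.** Keeping 180 evaluable men after losing 35 % needs 180 / 0.65 = 277. A total of 200 allows for a loss of 1 − 180/200 = 10 %.

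**Adequate-function men only.** 0.65 × 100 = 65 per arm. SE = 4.0 × √(2/65) = 0.702, and 1.51 / 0.702 = 2.15. Exact power is 69 %.

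**All 200 men.** Difference = 1.51 × (0.65 + 0.35f); SE = 4.0 × √(2/100) = 0.566.

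| f | Difference | Difference / SE | Exact one-sided power |
|---|---|---|---|
| 0 | 0.98 | 1.74 | 53 % |
| 0.25 | 1.11 | 1.97 | 62 % |
| 0.50 | 1.25 | 2.20 | 71 % |
| 1 | 1.51 | 2.67 | 85 % |

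**Break-even for restriction.** At equal SD, 65 per arm at the full difference matches 100 per arm when 0.65 + 0.35f = √0.65 = 0.806, so f = 0.156 / 0.35 ≈ 0.45.

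**f needed for 80 % in all men.** Required difference = 2.487 × 0.566 = 1.41; 1.41 / 1.51 = 0.93; (0.93 − 0.65) / 0.35 ≈ 0.8.

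**Recruiting more does not cure dilution.** With 139 per arm, all compared and f = 0, power is about 65 %.

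**Wider spread on raw follow-up scores.** Assume that poor-function men also score lower (mean m of 5 to 11, SD s of 3 to 4; neither is in the document), f = 0, and 15.86 is the mean of the two planned group means. Variance = 0.65 × 16 + 0.35s² + 0.35 × 0.65 × (15.86 − m)².

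- m = 11, s = 3: 10.4 + 3.15 + 5.37 = 18.9; SD 4.35; power 48 %.
- m = 5, s = 4: 10.4 + 5.6 + 26.8 = 42.8; SD 6.54; power 28 %.

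**Change scores.** If 4.0 is also the SD of change in adequate-function men, poor-function men do not change at all, and any gap in mean change between the two kinds of men is ignored, then SD = √(0.65 × 16) = 3.22. The difference of 0.98 then gives 69 % power, the same as restriction.

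**The case against.** The strongest reply is that the conflict is read partly from silence. No sentence says that every treated man enters the IIEF comparison. The only test named for questionnaires is a paired one, baseline against follow-up. The objective covers several instruments at once, and a fuller protocol or analysis plan may define the set. This stands as a limit: a reader might infer that the article commits to comparing IIEF in all men, and it does not. What remains is that the printed sizing and the printed, unrestricted objective do not describe the same comparison.

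A reader might also infer that men with poor function cannot decline and would count as free of erectile side effects in both arms. The text does not support that. It says *poor*, not absent, function; 35 % is a general-population figure; and no scoring rule is given. The advantage of restriction depends on this point and is gone at f of about 0.45.

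The cited HIFU studies may already have included such men. If so, 1.51 is partly diluted and multiplying by 0.65 overcorrects. The document does not settle this.

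The powers of 28 to 48 % need assumed means and unadjusted raw scores. Baseline adjustment or change scores would recover much of that loss, so these figures are a sensitivity range.

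Finally, a reader might fear a false claim that the two ablations are equivalent. No equivalence or non-inferiority conclusion is planned, and the group analyses are labelled hypothesis-generating. The difficulty is one of interpretation and power.

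**Conclusion.** The point holds in this limited form: the sizing sets aside men with poor baseline function, while eligibility, randomisation, objective and analysis include them without restriction. With the plan's difference and SD, the one-sided 5 % test and the 35 % share, power is 69 % if only adequate-function men are compared. It is about 53 to 71 % if all 200 are compared and the poor-function men show none to half of the effect. It is lower still on unadjusted raw scores if they also score lower. The stated 80 % is reached in all 200 men only if poor-function men show about 80 % or more of the full arm difference, which sits badly with making an allowance for them. The size rests on the assumed f and on a general-population share. The mismatch itself rests on neither.

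**What to change.** In the primary objective and the statistical analysis:

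- State that the focal-versus-extended IIEF comparison on which the trial is sized is made in men with adequate baseline erectile function.
- Define them by a baseline cut-off fixed before unblinding, on the IIEF version actually administered. The 45-point stratum refers to a total IIEF score and the sizing to IIEF-5, so the stratum cannot simply be carried over; reconcile the two.
- Report the all-patient comparison, adjusted for baseline IIEF, as supportive.
- Keep all randomised men for CTCAE, IPSS, pads and EPIC.
- Restate the analysed number (0.65 × 200 = 130 if the 35 % applies) and the power (about 69 %). Keeping 90 evaluable men per arm would need 277 in total.

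The cost is a few sentences and no new data. Because the subset is defined at baseline, the randomised comparison is preserved. The downside is that the IIEF conclusion applies only to men with function to lose, and the gain in power over an all-patient analysis disappears if poor-function men carry about 45 % or more of the effect.

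### The 35% allowance for poor baseline erectile function was not applied in full: it takes 180 men to about 277, and the target of 200 covers only a 10% loss

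*Protocol article*

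**What the plan says.** All the inputs stand in the protocol article, section Sample size calculation.

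- Assumption for the focal arm: "the mean IIEF score is 16.61 (SD 4.0) in Group A (focal ablation".
- Assumption for the extended arm: "the mean IIEF score is 15.1 (SD 4.0) in Group B (extended ablation".
- Test: "A two group Wells-Satterthwaite *t*-test of equal means and unequal variances were used to calculate the sample size". On direction: "The one-sided (one-tailed) test was used".
- Error rates: "With an α level of 0.05 and power of 80 % (1-β".
- Base result: "the sample size required was at least 90 men per group".
- Stated adjustment: it allows for 35% of men, a share taken from the general population over 50, "having poor baseline erectile function [36], and therefore aim to recruit at least 200 men in total".
- The figure of 200 recurs in the Abstract, Background, Population and Discussion.

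**The concern.** The section gives a base number, an allowance and a final target, and presents the target as the result of applying the allowance to the base. A reader can check that step, and it fails: moving from 180 to 200 is far too small a change for a 35% allowance.

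Erectile function is the one outcome on which the trial is sized. A reader will take 200 recruits as delivering 80% power even after men with poor baseline function are allowed for. If that is untrue, an IIEF comparison with no significant difference would be over-read as evidence that extended ablation costs no more erectile function than focal ablation. That is close to the question the trial was set up to ask.

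**Working it through.** **Inputs** (Sample size calculation): difference 16.61 − 15.1 = 1.51; SD 4.0 in both groups; one-sided α = 0.05; power 80%; base 90 per group; allowance 35%; target 200. Equal allocation is my assumption; the article gives a single per-group number but no ratio.

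**Step 1. Reproduce the base number.**
- Normal approximation: n = 2 × SD² × (z₀.₉₅ + z₀.₈₀)² / difference² = 2 × 16 × (1.645 + 0.842)² / 1.51² = 86.8, so 87 per group.
- Noncentral t, with 2n − 2 degrees of freedom because the SDs and group sizes are equal: 88 per group.
- The two-sided version gives 111 to 112 per group and does not match.

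So the 90 is the one-sided t-test number, lightly rounded up. The 35% is not already inside it.

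**Step 2. Apply the allowance.**

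| Calculation | Total recruits |
|---|---|
| 180 / (1 − 0.35) | 276.9, about 277 |
| 90 / 0.65 = 138.5, rounded up to 139 in each arm | 278 |
| Unrounded base: 176 / 0.65 | about 271 |
| Incorrect form: 180 × 1.35 | 243 |
| Stated target | 200 |

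None of these gives 200. The loss that 200 recruits can absorb while keeping 180 is 1 − 180/200 = 10%.

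**Step 3. What 200 recruits deliver, by the share giving no information on the IIEF.** One-sided t-test, difference 1.51, SD 4.0:

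| Uninformative share | Men per group | Power |
|---|---|---|
| 0% | 100 | 84.5% |
| 10% | 90 | 81.0% |
| 20% | 80 | 76.8% |
| 35% | 65 | 69.0% |

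For the 35% row: 200 × 0.65 = 130 men, 65 per group. The normal approximation gives 69.4%.

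**Step 4. Detectable difference at 65 per group, 80% power.** Noncentral t: 1.754. Normal approximation: 2.487 × 4.0 × √(2/65) = 1.745. About 1.75 points, against the planned 1.51.

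**Step 5. A further scenario.** Suppose the 35% are analysed but show no treatment difference, with SD still 4.0. Both are assumptions that the article does not state. The average difference becomes 0.65 × 1.51 = 0.98, and power at 100 per group is about 53%.

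**The case against.** Several points on the other side carry weight.

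- **Some adjustment was made.** The target did rise from 180 to 200. A reader might infer that the allowance was ignored altogether; the text supports only that it was not applied in full.
- **The 69% is conditional.** A reader might take it as the trial's actual power. The article does not say that men with poor baseline function are left out of the analysis. Table 1 does not exclude them, and randomisation is stratified on baseline IIEF, so men with low scores are expected to be randomised. The 35% is a general-population figure for men over 50, and the share among men meeting these eligibility criteria may differ. If all 200 count fully, power exceeds 80%. However, if they all counted fully there would be nothing to adjust for, and the section says an adjustment was made. The 35% is the protocol's own planning figure, and 200 recruits keep 90 per group only if the share is 10% or less.
- **The consequence is softened.** The Statistical analysis section calls the group analyses hypothesis-generating, and 200 is given as a minimum. Neither makes the stated allowance consistent with the stated target.
- **The test in the power calculation may not be the test run.** The Statistical analysis section names a two-tailed signed rank test of baseline against follow-up, and no one-sided comparison between groups. A two-sided t-test at 65 per group would have about 57% power. Any restated figure must therefore carry its one-sided label.

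A reader might also infer that dropout was forgotten. The documents do not support that: a condensed article may leave a dropout allowance to the full protocol.

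**Conclusion.** The point stands as an internal contradiction in the sample size section. A base of 180, a 35% allowance and a target of 200 cannot all hold; the allowance leads to about 277, and the target accommodates 10%. That conclusion needs no assumption beyond the article's own figures.

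The effect on power depends on what happens to the men with poor baseline function. At the planning share of 35%, all uninformative, one-sided power is about 69%, so the chance of missing the planned difference is about 31% rather than 20%. Power is about 84.5% if every recruit counts with the same difference and SD. The figure of about 53% rests on a zero effect in these men and an unchanged SD, so it is only an illustration of how far the answer could move. The documents do not settle which case applies, and the article should.

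**What to change.** In the Sample size calculation section:

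1. State how the 35% was used: whether men with poor baseline erectile function are excluded from the IIEF comparison, analysed with the rest, or handled in another way.
2. Delete the claim that 200 already includes a 35% allowance.
3. Restate the power and detectable difference that 200 recruits deliver for the population actually analysed, labelled as one-sided and conditional on the uninformative share. For example: 10%, 81%; 20%, 77%; 35%, 69%, the last with a detectable difference of about 1.75 IIEF-5 points. If all randomised men are analysed, give the power for that population and state the difference and SD assumed in it.

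This is a change of wording. It needs no extra enrolment and no change to procedures. The only downside is a less favourable stated power.

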#### Statistical analysis

Data will be collected using the Data Management System of CROES. The validated questionnaires will be analysed with standard methods. Maximum and minimum values will be set according to the extremes of questionnaire item scales. Categorical outcomes will be reported as point estimates with binomial 95 % CIs to demonstrate level of precision. Wilcoxon signed rank test (two-tailed) will be used to assess differences between continuous variables that were not normally distributed (PSA and questionnaire scores), measured at baseline and at the subsequent follow-up visit. Changes over time will be reported with box-and-whisker plots. The group analyses will be hypothesis-generating and we will run statistical tests of significance.

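### The test named for the primary questionnaire scores is a two-tailed paired before/after test, which conflicts with the between-group objectives and the one-sided two-group t-test that sized the trial

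*Protocol article*

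**What the plan says.** The protocol article addresses this point in three places.

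- **Study objectives, Primary.** There are two objectives, both contrasts between the randomised groups: "To evaluate the differences in side effects of patients treated with focal vs extended ablation of PCa with IRE" (CTCAE, IIEF, IPSS, pads) and "To evaluate the differences in quality of life of patients treated with focal vs extended ablation of PCa with IRE" (EPIC, VAS pain, length of stay).
- **Sample size calculation.** The trial is sized on IIEF-5, with means of 16.61 in Group A (focal) and 15.1 in Group B (extended) and SD 4.0 in each. The test is between groups: "A two group Wells-Satterthwaite *t*-test of equal means and unequal variances were used to calculate the sample size". It is also directional: "The one-sided (one-tailed) test was used, because this rejects the null hypothesis for differences in a single direction". With α 0.05 and 80% power the section states at least 90 men per group, and the recruitment target is 200 in total.
- **Statistical analysis.** For PSA and the questionnaire scores the named test is: "Wilcoxon signed rank test (two-tailed) will be used to assess differences between continuous variables that were not normally distributed", these being "measured at baseline and at the subsequent follow-up visit". Categorical outcomes are to be given as point estimates with binomial 95% intervals, and changes over time as box plots. The section closes: "The group analyses will be hypothesis-generating and we will run statistical tests of significance".

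**The concern.** The Wilcoxon signed rank test works on paired differences, here each patient's follow-up score minus his own baseline. It asks whether scores moved over time. It does not ask whether they moved more in one arm than in the other, which is the question the trial randomises patients to answer.

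So the one analysis test attached to IIEF, IPSS and EPIC does not address the primary objectives and is not the test the trial was powered for. The closing sentence may also give the arm comparison an exploratory status, although the sample size section powers that comparison at 80%.

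What is at stake is the trial's main inference. As published, the test, the sidedness and the confirmatory status of the focal-versus-extended comparison could each be settled after the data are seen. A before/after change within an arm also mixes the treatment effect with anything else that changes over time, which the randomised comparison is there to remove.

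**Working it through.** **Inputs from the Sample size calculation section.** Means 16.61 and 15.1, so the difference is 1.51; SD 4.0; α 0.05; power 80%; 90 per group; 200 in total. Equal allocation is assumed from the equal group sizes, because no ratio is stated.

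**Step 1: which test does the stated 90 come from?** Normal approximation: n per group = 2 (z_α + z_β)² SD² / difference².

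- One-sided: 2 × (1.645 + 0.842)² × 16 / 1.51² = 197.9 / 2.280 = 86.8, so 87. The t-distribution version gives 87.45, so 88.
- Two-sided: 2 × (1.960 + 0.842)² × 16 / 1.51² = 251.2 / 2.280 = 110.2, so 111. The t-distribution version gives 111.12, so 112.

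The stated 90 lies within two patients of the one-sided two-group t-test and far from the two-sided one. The powered test is therefore between groups and one-sided.

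**Step 2: set the powered test beside the test named for analysis.**

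| | Sample size calculation | Statistical analysis |
|---|---|---|
| Contrast | Group A vs Group B | baseline vs follow-up, same patient |
| Method | unequal-variance t-test | signed rank test |
| Sidedness | one-sided | two-tailed |
| Status of group comparison | powered at 80% | hypothesis-generating, if group means arm |

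**Step 3: what the sidedness is worth.** The standardised difference is 1.51 / (4 × √(2/n)): 2.532 at n = 90 and 2.669 at n = 100. Subtracting 1.645 or 1.960 and taking the normal probability gives the approximate power; the t-distribution values follow in brackets.

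| Per group | One-sided | Two-sided |
|---|---|---|
| 90 | 81.3% (81.0%) | 71.6% (71.2%) |
| 100 | 84.7% (84.5%) | 76.1% (75.7%) |

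If a rank-sum test replaces the t-test, at an assumed relative efficiency of 0.955, the requirement is 87 / 0.955, so 92 per group one-sided, or 111 / 0.955, so 117 two-sided.

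**Step 4: why within-arm tests cannot stand in for the comparison (illustration only).** Simulation of 4,000 trials with 90 per arm, normal scores and SD 4. The baselines and the baseline-to-follow-up correlation of 0.5 are assumptions; the article gives neither. Each arm gets a two-tailed signed rank test at 0.05, and the arms are compared by a two-sided rank-sum test on follow-up scores.

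| Assumed baseline | Follow-up A / B | Signed rank significant, A / B | The two arms' verdicts differ | Rank-sum rejects |
|---|---|---|---|---|
| 18.5 | 16.61 / 15.1 | 99% / 100% | 1% | 70% |
| 17.5 | 16.61 / 16.61 | 54% / 54% | 50% | 5% |
| 18.5 | 16.61 / 16.61 | 99% / 99% | 2% | 5% |
| 18.5 | 15.1 / 15.1 | 100% / 100% | 0% | 5% |

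In the first row a real difference exists and the paired tests do not show it. In the second there is no difference, yet the verdicts differ half the time. For two equal arms the disagreement rate is 2p(1 − p), which cannot exceed 50%: 2 × 0.54 × 0.46 = 0.50. The second row is thus the worst case, and the last two rows show that the rate almost vanishes under a larger shared decline.

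**The case against.** A reader might infer that the primary objective goes untested and that the trial will produce no between-arm estimate. The documents do not support that. The analysis section ends by promising significance tests in the group analyses. If these are the arm comparisons, a between-arm test is planned but not named. If the phrase means subgroups, no arm comparison is promised there, but the conflict over confirmatory status falls away. The wording does not settle which is meant.

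It would also be too much to say that the paired test is the only test in the document. The sample size section names a two-group t-test on IIEF, though as the basis for sizing and not as the analysis.

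The article condenses a fuller protocol approved by the ethics board, and an analysis plan may exist. An unnamed between-group test could properly sit there and would not by itself be a finding. A test of change from baseline is also a legitimate companion analysis. Similarly, the sentence on categorical outcomes does not exclude a comparison between arms.

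Finally, nothing in the article proposes to judge the arms by whether one changes significantly and the other does not, so the 50% figure is not an error rate of this plan.

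All of that stands. It does not remove the conflict between what is actually stated: a two-tailed paired test for the scores that carry the primary objectives, beside between-group objectives and a one-sided two-group sizing test. A fuller document could add the right analysis, but these published sections would still disagree.

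**Conclusion.** The concern holds in a limited form. Within the Statistical analysis section, the only test named for the questionnaire scores cannot compare focal with extended ablation. It differs from the powered test in contrast, method and sidedness. The between-group test is unnamed, and its status is put in doubt if the group analyses are the arm comparisons.

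The measurable consequence concerns sidedness. At the article's own difference and SD, 90 per group gives about 81% power for a one-sided two-group t-test but about 71% for a two-sided one (76% at 100 per group). This rests on equal allocation and on the article's means and SD. The simulated disagreement between within-arm verdicts, anywhere from 0% to 50% over the scenarios tried, depends on assumed baselines, declines and correlation. It only explains why a paired test is no substitute.

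**What to change.** - State the between-group difference in IIEF-5 (Group A minus Group B), with a confidence interval, as the primary analysis. Use the two-sample unequal-variance t-test of the sample size section, or a rank-sum test with a shift estimate if the scores are clearly skewed. Table 2 schedules the questionnaire at many visits, so name the visit in the same sentence.
- Keep the signed rank test as description of change within each arm.
- Report categorical outcomes as between-group differences with 95% confidence intervals.
- Limit the hypothesis-generating label to comparisons other than the primary one, and say whether the group analyses are arms or subgroups.
- State one sidedness for the sample size and the analysis. If one-sided is kept, about 81% power at 90 per group stands, and the matching interval is a one-sided 95% bound (or a two-sided 90% interval). If two-sided, restate power as about 71% at 90 per group and 76% at 100.

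The cost is wording, with no new data. The one real downside is that a two-sided choice makes the stated power less favourable: restoring 80% would need 2 × 112 = 224 analysable men, more than the 200 planned.
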